#### Dropout criteria

The following are the dropout criteria:
Patients who withdraw their consent during the studyPatients who cannot be contacted at all for follow-up

### Who will take informed consent? {26a}

Informed consent will be obtained by the principal investigator or their sub-investigators.

Although this study focuses on delivery by CS (both elective and emergency) and not by the vagina, we are inviting all expecting pregnant women attending Goulburn Valley Health Obstetrics and Gynaecology Department to participate, since emergency CS delivery with intended vaginal delivery is mostly unpredictable. Patients will be approached to participate in the study by one of the sub-investigators or the principal investigator from the treating team. The investigator will be responsible for providing each patient with a participant information and consent form (PICF) about the study’s purpose and procedures, foreseeable benefits and potential risks of participation, information on data protection procedures and option to withdraw from the study at any time and without any given reason, which should be read by the patient. The investigator will answer any questions the patient may have, and both the patient and investigator will sign the informed consent form to indicate the patient’s full understanding of the protocol. Written informed consent must be obtained for all participants prior to any trial-related procedures and is subject to prior confirmation that the inclusion/exclusion criteria during the eligibility assessment are met for the enrolment of the patient.

### Additional consent provisions for collection and use of participant data and biological specimens {26b}

In the PICF, the participants will be informed about the use and storage of personal data collected during their participation in the trial. The PICF also contains information concerning the personnel who can access personal data collected during this trial and the period that the data will be kept following the study’s completion. By signing the informed consent form, the participants agree to the terms addressed in the PICF.

This trial does not involve any collection or storage of biological specimens.

### Interventions

#### Explanation for the choice of comparators {6b}

Different antiseptics or cleansing without antiseptic have been practised inconsistently, and there is no clear evidence supporting which vaginally administered antiseptic solution is the most effective for preventing post-CS infections. The choice of comparators is based on the common variations of antiseptic solutions for vaginal preparation before CS. No toileting was chosen as a control to best determine any effects of the interventions.

#### Intervention description {11a}

Patients undergoing elective or emergency CS are randomised to receive either of the following:
1% povidone iodine antiseptic solution for vaginal cleansing immediately prior to CS (intervention)Chlorhexidine antiseptic solution (aqueous) for vaginal cleansing immediately prior to CS (intervention)No vaginal cleansing immediately prior to CS (control)

All the enrolled patients’ skin preparation will follow the same procedure and use of the same material of similar quantity (chlorhexidine). All enrolled patients will receive the same health education and wound care advice from the treating team.

#### Criteria for discontinuing or modifying allocated interventions {11b}

If, for any reason, a study intervention is not administered at the scheduled time, immediately prior to CS, it may not be administered later, and the patient will be withdrawn from the study. A patient may also be withdrawn from the study for the following reasons: (1) development of intrapartum pyrexia as a result of syntocinon drip, prolonged labour or obstructed labour intrapartum pyrexia and positive m/cs swab test; (2) withdrawal of consent from the study; (3) lost to follow-up; or (4) vaginal delivery is successful and emergency CS is not necessitated.

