#### Exclusion criteria

The following are the exclusion criteria:
Patients having signs of chorioamnionitis, intrapartum pyrexia and other signs of infection will be excluded from the study.Patients who develop intrapartum pyrexia as a result of syntocinon drip, prolonged labour or obstructed labour and provided voluntary informed consent will be included in the study initially. Their placental swabs will be taken for microscopic examination, culture and sensitivity (mcs). They will be excluded from the study only if their swab results are positive for mcs.Face presentation.Vaginal delivery.Patients who have known allergies to iodine or chlorhexidine.

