### Implementation {16c}

A third party, not involved in the assignment or care of the trial participants, will generate the permuted blocks for randomisation and place the assigned treatments in the sealed envelopes. Study investigators will lead participant recruitment, informing participants of all the trial procedures and obtaining their informed consent before the initial inclusion in the study. Study investigators will confirm the eligibility of the participant prior to any study procedures being undertaken. Prior to CS delivery, participants will pick one of the opaque sealed envelopes at random and pass it on to the treating team. Upon opening of the envelope, which designates chlorhexidine or 1% povidone iodine or no vaginal cleansing, the treating team will administer the allocation immediately prior to CS.

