### Plans to promote participant retention and complete follow-up {18b}

During participant recruitment, the purpose and importance of the trial will be explained via the study team and PICF. The participant has the right to withdraw from the trial at any time and for any reason without prejudice to her medical care and routine treatment by the treating team or at the institution. If a participant withdraws from the trial before concluding the study and since the data will be recorded anonymously, an intention-to-treat analysis will be performed for such patients’ data. If a patient is withdrawing their consent during the conduction of the trial and unwilling to consent for utilising already collected data and if these specific data can be retrieved, the investigator will delete the data accordingly.

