## Statistical methods

### Statistical methods for primary and secondary outcomes {20a}

Baseline characteristics of participants including demographic characteristics, morbidity information with severity, current medication/management and satisfaction towards the current management will be compared using the *t*-test or and *χ*^2^ tests for categorical variables to assess the success of the randomisation. Summary statistics will be presented for all three groups’ infection information. BMI will be calculated using the weight and height of the participants. If required, the analysis will be performed following the ‘intention-to-treat’ analysis method. Primary and secondary outcomes will be compared using ANOVA. Where appropriate, logistic regression analyses will be used to compare the outcomes separately for interventions versus the control group. All data will be entered in MS Excel, and all statistical analyses will be performed using the STATA 11.0 statistical package.

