### Methods in analysis to handle protocol non-adherence and any statistical methods to handle missing data {20c}

No imputation of missing data will be performed for statistical analysis.

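### Randomised women are removed for uncleansed delivery (possible only in the antiseptic arms) and for a positive placental swab, and intention-to-treat is conditional, so the primary comparison can be biased

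*Protocol article*

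**What the plan says.** All references are to the protocol article.

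- **Timing of allocation.** Implementation {16c}: "Prior to CS delivery, participants will pick one of the opaque sealed envelopes at random and pass it on to the treating team". The envelope is then opened and "the treating team will administer the allocation immediately prior to CS". Only participants are blinded {17a}.
- **Non-administration.** Criteria for discontinuing {11b}: if for any reason the study intervention is not given when scheduled, "it may not be administered later, and the patient will be withdrawn from the study".
- **Control arm.** Intervention description {11a} labels the two antiseptics as interventions and no cleansing as the control.
- **Swab result.** Under the exclusion criteria, women whose pyrexia arises from a syntocinon drip or from prolonged or obstructed labour enter the study and have a placental swab. "They will be excluded from the study only if their swab results are positive for mcs". Section {11b} repeats this as a reason for withdrawal.
- **Analysis set.** Statistical methods {20a}: "If required, the analysis will be performed following the" intention-to-treat method. No criterion says when it is required. Section {18b}, on a participant who withdraws before the study ends: "an intention-to-treat analysis will be performed for such" data. The same section provides for deletion of data where a woman refuses its use.
- **Missing data.** Section {20c}, which covers both non-adherence and missing data: "No imputation of missing data will be performed for statistical analysis".

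**The concern.** Both removals happen after the allocation has been drawn, and each can depend on the arm.

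The non-administration rule does so by construction. An antiseptic-arm woman can fail to receive her allocation and leave the study; a control woman cannot. If the women missed are at higher than average risk, they leave the antiseptic arms while their counterparts stay in the control arm. The background section {6a} reports higher infection rates with ruptured membranes and with CS in labour, so average risk among those missed should not be taken for granted.

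The swab rule does so if cleansing changes the chance of a positive result. It then selects the analysed women on something measured after treatment, and those selected out are plausibly near the top of the risk range for endometritis, the primary outcome.

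A firm intention-to-treat rule would neutralise both removals, but the two statements on it do not agree. An analysis plan written later could not fully repair this, because it cannot recover outcomes that were not collected after withdrawal.

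**Working it through.** **Step 1: planning value.** The sample size section {14} uses P1 = 0.08, P2 = 0.04, Z values 1.96 and 0.84. Its formula gives ES = 0.04/√(0.08 × 0.92) = 0.1474 and n = (2.80/0.1474)² = 360.6, so 361 as stated. The 8% control rate is used below. It is the plan's figure for post-CS infection overall, not for endometritis alone.

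**Step 2: which arms the non-administration rule can reach.** {11b} requires that a study intervention was not administered. {11a} gives the control arm nothing to administer. {16c} puts allocation before administration. As written, the rule therefore acts after randomisation and in two of the three arms.

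**Step 3: effect of that rule when there is no true effect.** Let every arm have risk p = 0.08. Let a share f of an antiseptic arm be uncleansed and removed, with risk r. Then

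retained risk = (p − f·r)/(1 − f)

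The control arm stays at 8%. The document gives neither f nor r; these are assumptions.

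| f | r | retained antiseptic risk | spurious relative reduction |
|---|---|---|---|
| 5% | 15% | (0.08 − 0.0075)/0.95 = 7.63% | 4.6% |
| 5% | 20% | (0.08 − 0.0100)/0.95 = 7.37% | 7.9% |
| 10% | 15% | (0.08 − 0.0150)/0.90 = 7.22% | 9.7% |
| 10% | 20% | (0.08 − 0.0200)/0.90 = 6.67% | 16.7% |

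Over a wider range, with f from 2% to 15% and removed women at 1.5 to 3 times average risk, the spurious risk ratio runs from 0.99 to 0.65. If r = p, the formula returns p and the risk ratio is 1.00.

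**Step 4: effect of the swab rule when there is no true effect.** Let w be the share of women with the qualifying pyrexia, q the share of those with a positive swab, and s the infection risk in swab-positive women. Then

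retained risk = (p − w·q·s)/(1 − w·q)

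All three inputs are assumptions. The document also gives no swab time; that the swab follows cleansing is inferred from its being placental and from cleansing preceding CS.

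- w = 5%, q = 50% control and 30% antiseptic, s = 20%: 0.0750/0.975 = 7.69% control and 0.0770/0.985 = 7.82% antiseptic; risk ratio 1.02.
- w = 10%, q = 50% control and 25% antiseptic, s = 40%: 0.0600/0.950 = 6.32% control and 0.0700/0.975 = 7.18% antiseptic; risk ratio 1.14.
- q equal in all arms: risk ratio 1.00.

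If cleansing lowers positivity, this route works against the antiseptics, opposite to step 3.

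**Step 5: the intention-to-treat statements side by side.** {20a} makes the method conditional without saying on what. {18b} is firm, but its subject is a participant who withdraws. Neither says that a woman removed under {11b} or the exclusion criteria is still followed or analysed, and {20c} rules out imputing her outcome.

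**The case against.** **The bias is small against sampling error.** In step 3 it is 0.4 to 1.3 percentage points. With 132 per arm, the standard error of a two-arm difference at 8% is √(2 × 0.08 × 0.92/132) = 3.3 points, so the bias is about 0.1 to 0.4 standard errors. In the worst of the four cases, two-sided type I error rises from 5% to about 7%. This stands and limits the size claimed. It does not excuse a systematic error that costs little to remove.

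**Few women may be missed.** The envelope is drawn shortly before CS, and women too urgent for cleansing may never be randomised. That is possible; the documents give no rate. That the missed women would be the most urgent cases is likewise an inference.

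**The two intention-to-treat statements can be reconciled.** The condition in {20a} may mean only that the method applies if such cases arise. This is a fair reading, so the conflict is closer to ambiguity. It leaves open whether women removed by the investigators are covered.

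**Stronger readings that the documents do not support.**

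- A reader might infer that staff who know the allocation decide whether a pyrexia qualifies. The exclusion criteria, {16a} and {16c} place inclusion and eligibility before assignment, with the envelope opened just before CS, and the swab is prescribed for these women. Attribution would normally precede knowledge of the arm.
- A reader might set the planned 10% dropout, about 13 women per arm, against roughly 9.5 expected control events. That compares women with events: 13 women at 8% carry about one event. The 9.5 (8% of about 119) is also already net of dropout.
- A reader might infer that outcomes of women missed by telephone are ignored. The dropout criteria cover only women who cannot be contacted at all, and {30} and {18a} already plan follow-up at hospital presentations to day 28. What remains is to state that such outcomes are kept in the analysis.

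**Conclusion.** The point holds as a risk of bias. The non-administration rule removes randomised women from the antiseptic arms only. The swab rule removes women on a result that may depend on arm, given the inference that the swab follows cleansing. The analysis set is not fixed firmly enough to undo either.

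Under the step 3 assumptions the spurious relative reduction is 5–17% (observed antiseptic rate 6.7–7.6% against 8%). It is nil if the removed women are at average risk.

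It would be tempting to conclude that the rules are bound to produce an apparent benefit. The documents do not support that: the swab route may favour control or be neutral, the two mechanisms can partly cancel, and the net direction is unknown. What is lost is the assurance that the expected risk ratio is 1.00 when the treatments do nothing. Because the loss affects the primary comparison and the remedy is mostly wording, it should be corrected.

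**What to change.** 1. In {11b}, replace withdrawal for non-administration with a statement that the allocated treatment was not received and that follow-up and outcome collection continue to day 28. The rule on whether late cleansing may be given is clinical and is left as it stands.
2. In {20a}, delete the condition on intention-to-treat and reconcile the section with {18b}. Suggested text: *The primary analysis includes every randomised woman who has a CS, in her allocated arm, whether or not cleansing was given and whatever the swab result, except where she withdraws consent to the use of her data.* The exception preserves the deletion provision in {18b}.
3. Align the exclusion criteria with this, so that a positive swab does not take a randomised woman out of the primary analysis.
4. State that outcomes captured at hospital presentations are kept for women who cannot be reached by telephone.
5. Report exclusion of uncleansed women and of swab-positive women only as sensitivity analyses.

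The cost is a protocol amendment, a little more analysis work, and slight dilution of the estimated effect by women who were not cleansed.

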#### Strategies to improve adherence to interventions {11c}

The following measures will be, and or have been, taken to improve adherence to interventions and follow-up:
All participants will be informed of the study procedures, as well as potential benefits and risks to make them fully understand the significance of their involvement in the study.Inform the participants about the detail of the follow-up period which is relatively short, 28 days follow-up from the day of CS.Provide adequate details to the participants about the low or limited burden and inconvenience of data collection.

#### Relevant concomitant care permitted or prohibited during the trial {11d}

There will be no restrictions regarding concomitant care during the trial.

#### Provisions for post-trial care {30}

All patients will return to standard care after the trial. All the patients included in the study will be followed up for a period of 28 days for the outcome signs and symptoms. We will follow up the patients telephonically on the 14th and 28th post-operative days and also during any hospital presentations or admissions until 28 days post-CS.

### Outcomes {12}

#### Primary outcome

The primary outcome is endometritis: defined as tympanic temperature > 38 °C with uterine tenderness and/or foul-smelling vaginal discharge within 28 days of post-CS.

#### Secondary outcomes

The following are the secondary outcomes:
Post-operative fever: defined as tympanic temperature > 38 °C at any point until 28 days post-CSWound infection: defined as itch, redness, pain, swelling and collection of purulent discharge at the surgical incision site within 28 days post-CSReadmission with infection: defined as the representation of post-CS patients to the hospital within 28 days post-CS with surgical site infection or related infective complications

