#### Assessment of infection

A third person with adequate clinical acumen independent to the project will assess the post-CS infection to reduce any potential bias, for example, the obstetrics and gynaecology consultant on call and obstetrics and gynaecology registrar.

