### Sample size {14}

We assume that the interventions will improve the rate of infection including post-operative infective complications (within 28 days post-CS) by 50% compared to the control. Thus, for sample size estimation in this study, we set *P*_1_ = 8% (as per overall prevalence of post-CS infection range 3–15%), *P*_2_ = 4%, significance level = 5% and the study power = 80%.

Therefore,
$$ n\ge {\left(\frac{Z_{\alpha }+{Z}_{\beta }}{\mathrm{ES}}\right)}^2 $$$$ \mathrm{ES}=\frac{P_1-{P}_2}{\sqrt{P_1\left(1-{P}_1\right)}} $$

*n* ≥ 361

Here, *Z*_*α*_ = 1.96, *Z*_*β*_ = 0.84, *P*_1_ = 0.08, *P*_2_ = 0.04 and *P*_1_ − *P*_2_ = 0.04.

Considering 10% dropout, the study will require recruiting approximately 396 participants for all the groups (*n* = 132 in each group) over a period of 16 months to adequately test the assumption.

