## Data collection and management

### Plans for assessment and collection of outcomes {18a}

A predeveloped questionnaire will be completed with patients’ socio-demographic characteristics and required clinical and pregnancy-related information. All the fever, infection and readmission-related information such as duration of artificial rupture of membrane/spontaneous rupture of membrane, duration of labour, BMI, gestational diabetes mellitus (GDM) with current diet or insulin regime, duration of surgery, estimated blood loss (EBL), previous CS (1/2/3) of elective/emergency nature and vaginal examination at CS will be completed from either the patients or their record or at follow-up visits on the 14th and 28th post-operative days. All the patients included in the study will be followed up for a period of 28 days for the outcome signs and symptoms. Participants will be followed up over the phone fortnightly, at day 14 and day 28 post-CS. Participants will also be followed up during hospital presentations or admissions until 28 days post-CS. A third person with adequate clinical acumen independent to the project will assess the post-CS infection (primary and secondary outcomes) to reduce any potential bias, for example, the obstetrics and gynaecology consultant on call and obstetrics and gynaecology registrar. No identifying information but the aggregated data will be used for the analysis and interpretation.

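### The wound infection definition joins five signs with *and* and gives no counting rule: read as written it could miss true infections, and the event count depends on how the assessor reads it

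*Protocol article*

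**What the plan says.** All references are to the protocol article.

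- **Secondary outcomes.** Wound infection is "defined as itch, redness, pain, swelling and collection of purulent discharge at the surgical incision site", within 28 days of the caesarean. No words such as *any of* or *at least two of* appear.
- **Primary outcome.** Endometritis is "defined as tympanic temperature > 38 °C with uterine tenderness and/or foul-smelling vaginal discharge within 28 days of post-CS". Here the alternative between the two local signs is marked explicitly.
- **Assessment of infection.** "A third person with adequate clinical acumen independent to the project will assess the post-CS infection to reduce any potential bias"; the on-call consultant and the registrar are given as examples. No threshold is stated, and section {18a} and the oversight section repeat the arrangement without adding one.
- **Plans for assessment and collection of outcomes {18a}.** "Participants will be followed up over the phone fortnightly, at day 14 and day 28 post-CS", plus any hospital presentation or admission up to day 28.
- **Readmission with infection** (also under Secondary outcomes) is a return to hospital "within 28 days post-CS with surgical site infection or related infective complications". Surgical site infection is not defined separately, and its relation to the wound infection list is not stated.

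**The concern.** The definition can be applied in two ways, and neither serves the trial well.

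Taken literally, it is a conjunction of five signs. The *and/or* in the primary outcome strengthens this reading, because it shows that the authors mark alternatives where they intend them. One absent or unrecorded sign, itch for instance, is then enough to turn a frankly purulent wound into a non-event.

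Taken loosely, the list describes typical signs. A single non-specific sign at a healing incision, such as itch or redness, could then be counted.

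The assessor is left to choose. Different clinicians may classify over a planned 16 months of recruitment, and part of the information comes by telephone, where it is least clear how many signs a woman must report. If assessors differ, the wound infection rate partly measures their reading of the sentence. Section {17a} states blinding for participants only. The assessor is called independent but is not stated to be blinded, so an open threshold also leaves room for knowledge of the allocation to influence classification.

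**Working it through.** **The plan's own figure.** No figure is attached to the wound infection definition. The nearest calculation is the sample size, with P1 = 0.08, P2 = 0.04, Zα = 1.96 and Zβ = 0.84:

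- ES = 0.04 / √(0.08 × 0.92) = 0.1474
- n = (2.80 / 0.1474)² = 360.6, so 361, as stated.

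This does not depend on the wound definition, and nothing below alters it.

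**The wording side by side.** Endometritis requires fever plus (tenderness *and/or* discharge), so the combination is explicit. Wound infection requires itch, redness, pain, swelling *and* purulent discharge, so the only stated combination is all five. No other section of the article modifies this.

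**How much the strict reading could lose.** The document does not say how often each sign is present in a true wound infection. The following is therefore assumed, for illustration only: purulence is always present, and each of the other four signs is present and recorded with the same probability q, between 0.6 and 0.9. The share of true cases that meet all five signs is then:

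- under independence, q⁴;
- under any dependence, between max(0, 4q − 3) and q. The upper end is reached when the four signs always occur together.

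| q | Independent, q⁴ | Lowest possible | Highest possible |
|---|---|---|---|
| 0.6 | 13% | 0% | 60% |
| 0.7 | 24% | 0% | 70% |
| 0.8 | 41% | 20% | 80% |
| 0.9 | 66% | 60% | 90% |

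If purulence also had probability q, independence would give q⁵: 8% at q = 0.6 and 59% at q = 0.9.

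**When would more than half be missed?** Under independence with purulence always present, when q⁴ < 0.5, that is q < 0.5^(1/4) = 0.84. If the four signs always occur together, only when q < 0.5, which is outside the assumed range.

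**The loose reading.** If any one sign suffices, every true case in this illustration counts, because purulence is always present. Women with itch or redness at an uninfected incision would count as well. The document gives no basis for estimating how many.

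**The case against.** The strongest reply is that this is a list of typical signs handed to a qualified, independent clinician, and that nobody would refuse to call a purulent wound infected because it does not itch. That is plausible, and nothing in the article says that assessors will tick off five signs. But it rescues practice rather than the definition: on that account the outcome rests on judgement, and the written rule either does no work or contradicts the judgement. What stands is that the strict reading is one possible application, not an established one.

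Three stronger readings are tempting, and the document does not support them.

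- **That most wound infections would be missed.** A reader might infer this from the five-sign rule. It needs sign frequencies and correlations that the article does not give. Even within the assumed range, the share missed under independence runs from 34% to 87%, and it falls to 10–40% if the signs occur together. Redness, swelling and pain at one infected wound may well occur together.
- **That power falls by a stated amount.** The 8% and 4% in the sample size section are for infection overall, "as per overall prevalence of post-CS infection range 3–15"%. No wound infection rate is given. At 132 per arm, 8% against 4% gives only about 28% power in one pairwise comparison even if every case is captured; that shortfall belongs to the sample size, not to this definition.
- **That the fault carries into readmission and the overall infection rate.** The readmission outcome uses a broader phrase, and nothing says that a readmission must meet the five-sign list. Nor does any section build the overall rate from wound infection counts. A carry-over is possible but only inferred.

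It is also fair to say that the article is condensed and the questionnaire is not shown, so it may already record each sign. That bears on the cost of the fix. It does not bear on the defect, because the definition is stated, and stated badly, rather than left to another document.

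**Conclusion.** The point holds as a badly stated case definition for a secondary outcome. As written, all five signs are required, which could exclude true wound infections. Read loosely, a single non-specific sign could qualify. The article does not settle which applies, so the event count depends on the assessor.

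The size of the loss cannot be determined from the document. The illustration of 13–66% of cases captured under independence, rising to 60–90% if the signs occur together, rests on an assumed 60–90% frequency for each non-purulent sign and on purulence always being present. It shows that the choice of reading can matter a great deal; it does not estimate what will happen in this trial. The endometritis definition, and hence the primary outcome, is unaffected. Correction is advisable because it is cheap and a reported wound infection rate would otherwise be hard to interpret.

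**What to change.** 1. Replace the *and* list with an explicit combination rule that says which signs, and how many, make a wound infection, and that does not require all five. The sponsor should set the rule; the document gives no basis for a particular threshold. It should be fixed without reference to outcomes by arm.
2. State that the same rule applies to the telephone contacts on days 14 and 28 and to hospital presentations and admissions.
3. Record each of the five signs separately, if the questionnaire does not already do so, and report the strict all-five count and a broader count as a sensitivity analysis.
4. Add a short statement of whether surgical site infection in the readmission outcome means the same thing.

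The cost is a sentence or two in the protocol and, at most, five tick boxes. The downside is possible recoding of women already assessed. This may be more than trivial: planned recruitment ended in December 2021, before the article appeared in March 2022, and recoding is possible only where the scanned questionnaires or notes show the individual signs and can still be linked to the participant number. Where they cannot, the report should say which reading was used.
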